## Abstract

**Background:**

Transgender women have few interventions to support their HIV prevention and treatment outcomes in South Africa. Further, increased focus should be on intervention development that will reduce HIV transmission within HIV-discordant partnerships, especially for transgender women who navigate gender, sexuality, and relationship stigma. The Speaking Out and Allying Relationships (SOAR) intervention has been developed for sexual minority men to address these outcomes in South Africa. It is a behavioral intervention that is delivered in groups via videoconference to develop coping skills to manage HIV-related stress, assist with disclosure to partners, and establish and maintain safer sex practices with partners. Tailoring SOAR may be feasible for transgender women to support their HIV care while reducing transmission within their relationships.

**Objective:**

This study aims to (1) adapt SOAR for transgender women and test its usability, then (2) assess its feasibility.

**Methods:**

To achieve aim 1, we will use a human-centered design approach to tailor the existing SOAR intervention for transgender women. Interviews and a survey will be administered to transgender women (N=15) to assess intervention preferences. Findings will be used to tailor content like roleplays, scenarios, and media to align with transgender women’s lived experiences navigating HIV and relationships. Afterward, we will conduct a usability test with 7 (47%) of the 15 participants to determine intervention understanding and satisfaction. Participants will be transgender women living with HIV and in a relationship with a man who has unknown HIV status or is HIV-negative. All participants will be recruited using community-based approaches. In aim 2, we will examine SOAR feasibility using a 1-arm pilot study. Transgender women (N=20) will be recruited using aim 1 methods and eligibility criteria, with participants completing feasibility surveys and interviews, as well as behavioral and biomedical assessments.

**Results:**

Intervention adaptation began in May 2023 with interviews. Feasibility pilot testing was conducted with 14 transgender women, with study completion in January 2025.

**Conclusions:**

Transgender women need more intervention options that engage their relationships since these can present barriers to HIV treatment outcomes like hindering viral suppression in South Africa. Delivering an existing yet tailored intervention via videoconference expands its reach to transgender women and allows them to engage with others and learn new skills in a secure setting like their homes. SOAR has the potential to improve relationship dynamics and reduce violence, which will in turn enhance HIV treatment and prevention engagement.

**International Registered Report Identifier (IRRID):**

PRR1-10.2196/52121

## Introduction

### Background

HIV infections among transgender women are 2.2 higher than gay, bisexual, and other men who have sex with men in sub-Saharan Africa due to syndemics consisting of stigma and discrimination that perpetuate violence and victimization, limiting access to HIV prevention and treatment [1-4]. In South Africa, the HIV incidence for transgender women is 31 cases per 100-person years, with studies showing limited pre-exposure prophylaxis (PrEP) and antiretroviral therapy (ART) access and adherence. Based on other African studies, only an estimated 25% of transgender women are virally suppressed [5-7]. HIV prevalence among transgender women in South Africa mirrors the realities that they share with their peers in other Global South settings, with a 52% mean prevalence documented in 3 South African cities [8]. Transgender women’s health and safety remain compromised in South Africa, inhibiting their ability to engage in HIV services to lower transmission risk and improve their overall wellness, and compounding these health outcomes are poor relationship dynamics.

Being in an unhealthy or imbalanced relationship for transgender women can lower their HIV testing behaviors and increase rates of condomless anal intercourse with partners to create trust and intimacy [9-13]. Fear of partner rejection or loss and intimate partner violence may lead transgender women to limit or halt ART use to conceal their serostatus from partners [14-16]. Further, studies increasingly show that transgender women experience negative outcomes of relationship stigma (when partners fear being romantically associated with someone who is stigmatized), which in turn has hindered their ability to discuss HIV treatment with them [15,17]. Although studies with transgender women in South Africa are limited, in the United States, relationship dynamics for transgender women influence HIV risk, in the same ways they do for cisgender women and sexual minority men [17-21]. Additional factors hindering HIV prevention and treatment discussions that transgender may have with a partner include living with them, drug use, alcohol use, education level, and low self-efficacy to use condoms [18]. In sum, cisheteronormative social structures and power dynamics have been shown to result in increased marginalization, increased susceptibility to intimate partner violence, and increased risk of mental issues among transgender women, all hindering HIV prevention and treatment [22-24].

Further, transgender women are less likely to disclose their HIV status to other transgender women and sexual minority men within their social networks, increasing social isolation [25-27]. Only after being out of care and developing AIDS-related illnesses do transgender women disclose their HIV status to an immediate family member in order to secure support for their treatment, but this disclosure does not extend to partners [25,27]. Given a history of HIV care marginalization and discrimination, transgender women often possess inaccurate knowledge and skills in discussing with partners how PrEP and ART adherence, including “undetectable is untransmissible” (U=U) messaging, can work together to reduce transmission and in turn support relationship health [14-16]. Thus, transgender women have ongoing HIV-related stress without the skills to manage this stress and their disclosure to partners and others for support.

The benefits of social and partner support are significant for transgender women. Studies show that transgender women in committed relationships are less likely to engage in HIV-related high-risk behaviors, with researchers suggesting that relationship stability and emotional support lead to more consistent condom use and improved HIV prevention and treatment overall [28-30]. Specifically, higher relationship satisfaction, trust, and commitment were protective factors against HIV transmission among transgender women [17,31]. Additionally, 1 randomized controlled trial found that a social support group intervention further reinforced relationship-related protective behaviors among transgender women [32]. Therefore, a relationship-focused HIV intervention may support treatment and prevention outcomes for transgender women and their partners while garnering the support of family members earlier in their treatment journey.

To address this gap in interventions for transgender women living with HIV in South Africa, the aim of our study is to tailor our existing intervention, Speaking Out and Allying Relationships (SOAR) intervention, with them and then conduct a 1-arm pilot study to assess intervention feasibility in Eastern Cape, South Africa. Specifically, we will tailor SOAR and assess usability for content understandability and satisfaction (aim 1), and then evaluate its feasibility to include retention and any changes in behavioral and biomedical measures (aim 2). We hypothesize that participants will find SOAR feasible, acceptable, and safe to inform a larger efficacy study.

Our SOAR intervention is based on Healthy Relationships (HR), a 5-session, group-based evidence-based intervention to develop individual HIV disclosure risk assessment and safer sexual behavior skills with partners that have demonstrated efficacy in these outcomes in a range of settings [33,34]. The core elements of SOAR are to: (1) develop coping skills to manage HIV-related stress and sexually risky situations; (2) enhance decision-making skills for HIV disclosure to partners; and (3) establish and maintain safer sex practices with partners. The HR intervention was identified based on our preliminary research with sexual minority men and transgender women in South Africa [35]. Additionally, through this preliminary research, we demonstrated that transgender women are willing to complete HIV-related group work and have an interest in mHealth tools, like videoconference modalities, to learn skills in HIV treatment management and disclosure for support [36,37]. Moreover, harnessing high use rates of smartphones by transgender women for intervention delivery is feasible in South Africa [20,38]. Increased evidence shows that transgender women access web-based social networking sites and use SMS for social networking through mobile and smartphone technologies, creating the potential to tag on ART adherence interventions [39,40]. In our research, we found that HIV-positive sexual minority men and transgender women regularly use videoconferencing to support community networking across rural and urban settings, with 2-hour conversation events focused on HIV, sexuality, and gender [37]. Further, mHealth tools (SMS, chat rooms, and web-based video group interventions) for HIV prevention and treatment in South Africa are part of the national strategic plan [41]. As in the original HR, our SOAR intervention integrates media, scenarios, and roleplays for skill development, and these reflect the experience of South African sexual minority men living with HIV and in relationships. In addition to the standard 5 sessions, we include three 30-minute booster sessions to review action plans over 3 months.

### Theoretical Framework

Social cognitive theory serves as the framework for the intervention, which posits that cognition, behavior, and environment interact and influence health outcomes, like HIV risk reduction, disclosure, prevention, and ART adherence. SOAR aims to enhance coping skills for HIV-related stress, self-regulation of disclosure to include risk assessment, treatment, and prevention, and build self-efficacy in healthy behaviors and communication within relationships. Further, the intervention will provide a platform for participants to strengthen coping skills that will support and empower gender affirmation within relationship dynamics that may be experiencing stigma or risk of violence, or desire for improved relationship communication. Within the social cognitive theory model, the intervention will incorporate components such as HIV risk reduction education, treatment education including U=U, HIV prevention strategies like PrEP, and gender affirmation within the context of HIV. Skill-building activities for HIV communication and disclosure risk assessment will be conducted in a confidential group setting. By helping individuals plan for safe sex and consider HIV communication and disclosure to partners, the intervention aims to support ART adherence, empower participants with a sense of agency, and reduce negative feelings associated with their HIV status and internalized HIV stigma.

Our proposed tailoring of SOAR for transgender women is based on high interest to participate among those who attended community outreach activities for recruitment of sexual minority men as part of the original intervention. If this tailoring shows promise of feasibility, then we will conduct a larger randomized controlled trial to assess efficacy and implementation with local agencies that service sexual and gender minority communities in South Africa.

## Methods

### Study Design Overview

The study will use a 2-fold approach, beginning with intervention tailoring and usability assessment (aim 1) and then a 1-arm pilot study of the intervention (aim 2) to evaluate feasibility. Prior to study initiation, a study coordinator will be hired and trained in study procedures and the SOAR intervention and its delivery approach. The coordinator will be a member of the sexual and gender minority community in Eastern Cape and have a history of HIV program work. Coordinator training will include a review of sexual and gender minority health with a focus on HIV treatment and prevention barriers and facilitators for transgender women, gender-affirming care such as hormone replacement therapy, and relationship dynamics influencing HIV care. Additionally, the coordinator will complete training in good clinical practice and ethics and study procedures including data collection. Finally, the coordinator will be trained in the SOAR intervention which will include both didactic and simulation sessions until competency has been achieved. The study coordinator will conduct all study procedures with mentoring provided by the research team.

### Tailoring SOAR for Transgender Women

In aim 1, we will tailor SOAR by using a human-centered design approach. First, we will assess transgender women’s preferences and confirm their relationship dynamics regarding HIV. Then, we will evaluate the functionality of the intervention in a videoconference format (Zoom, Qumu Corp), and usability by gauging participants’ understanding and satisfaction with the SOAR intervention.

The study will be conducted in Buffalo City Municipality, Eastern Cape, South Africa. In this setting, there is a 46% HIV prevalence among transgender women who live in both urban and rural areas [8]. We will recruit transgender women (N=15) living with HIV and in a relationship for more than a month. Recruitment activities will be conducted by study staff at community events focused on transgender women and sexual and gender minorities. Study staff are members of the sexual and gender minority community and allies, and all completed LGBTQ competency training. Interested participants will be provided study explanation and invited to answer questions in the screening survey. Eligible participants will complete written informed consent in the language of their choosing (eg, isiXhosa, Afrikaans, English). The consent form will outline confidentiality and protections of participant information if they are interested in participating in the study. All participants will receive travel reimbursement and refreshments to complete study procedures.

### Preference Assessment and Integration

To assess transgender women’s preferences for the intervention, we will conduct in-depth interviews (IDIs). These interviews will delve into influences on HIV treatment including support and relationship dynamics, and gather feedback regarding various aspects of the intervention, including format and delivery. A semistructured question guide will ask questions in four domains: (1) HIV prevention and treatment knowledge; (2) relationship scenarios involving HIV disclosure and support for role-play development; (3) videoconference delivery preferences; and (4) positive representation of transgender persons in media (web-based, television, and movies) to show during the sessions. Each interview will be 60 minutes long, conducted in the local language (isiXhosa), transcribed verbatim, and translated for analysis. Findings from the analysis will be used to tailor SOAR to the contextual factors influential in HIV treatment and status disclosure for transgender women and to ensure representation of their empowering voices in the roleplays and videos to support skill building.

### Usability Testing

Usability testing will involve 2 tasks: pretesting and IDIs with participants. We will recruit 7 (50%) racially and relationship-length diverse transgender women participants from step 1 for pretesting. The pretesting phase will span 5 weeks, with 2-hour sessions each week. At week 8, 3 weeks after the last session, a group check-in session will be conducted via Zoom. Participants will receive SMS reminders for each session and the Zoom session link. All sessions will be completed together to foster positive group dynamics and will include a set of group rules for this purpose, and to protect the confidentiality of participants and their contributions during the sessions. The interventionist will monitor participant engagement throughout the pretesting and follow up with any missed sessions. Participants will provide their smartphone numbers for session reminders, self-assessment, action plans, and partner referrals delivered through Research Electronic Data Capture (REDCap; Vanderbilt University). The sessions and group check-in will be video-recorded for analysis, and participants will receive a data plan to facilitate their participation. After the pretesting phase, IDIs will be conducted with racially and relationship-length diverse participants over Zoom. The interviews will cover 6 usability domains for SOAR, including session functionality, timeliness and appropriateness, clarity of content delivery, document clarity and management, incomplete sessions, and technical transitions between sessions. The individual interviews in isiXhosa are expected to last approximately 50 minutes. Audio recordings of the interviews will be transcribed and translated into English for further analysis.

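### Usability interviews about a Zoom intervention are themselves held over Zoom, so women with connection, device or privacy problems risk being under-represented in the usability themes

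*Protocol article*

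**What the plan says.** Under Tailoring SOAR for Transgender Women, the article gives aim 1 this purpose: "we will evaluate the functionality of the intervention in a videoconference format (Zoom, Qumu Corp), and usability by gauging participants’ understanding and satisfaction". How well the Zoom format works is thus one of the things being measured.

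The Usability Testing section then sets out the following:

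- **Sample:** "We will recruit 7 (50%) racially and relationship-length diverse transgender women participants from step 1 for pretesting". (The Abstract gives 7 of 15 as 47%; the mismatch does not affect this point.)
- **Interview mode:** "After the pretesting phase, IDIs will be conducted with racially and relationship-length diverse participants over Zoom". No other mode is given, and the number interviewed is not stated.
- **Content:** six domains, among them session functionality and, at the end of the list, "document clarity and management, incomplete sessions, and technical transitions between sessions". Each interview lasts about 50 minutes.
- **Other contact and data:** "The interventionist will monitor participant engagement throughout the pretesting and follow up with any missed sessions", and "The sessions and group check-in will be video-recorded for analysis, and participants will receive a data plan to facilitate their participation".

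The aim 1 Data Analysis section derives preferences and usability from coded interview transcripts. It does not mention the recordings or the missed-session contacts. The Limitations section offers loan smartphones, or a tablet at a community site, for attending sessions.

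**The concern.** An interview meant to find out where Zoom failed requires a working Zoom call. A woman whose signal, phone or lack of private space disrupted the sessions may meet the same difficulty at the interview. Whether her usability data are observed then depends partly on the outcome being measured.

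The two stated diversity criteria do not counter this, because neither concerns attendance or technical trouble. With 7 women, each is 1/7 = 14.3% of the sample, so losing one or two could remove a whole type of problem from the themes. The usability work feeds the version of SOAR taken into the pilot, so a fault that nobody reports in aim 1 may be carried forward.

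**Working it through.** The plan has no figure to reproduce. The usability phase is qualitative and has no sample-size calculation. The check is a reading of the text, followed by an illustration of how large the effect could be.

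**Reading the text**

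1. What is tested: functionality in the videoconference format (Tailoring SOAR for Transgender Women).
2. How it is learned: transcripts of interviews held over Zoom (Usability Testing; Data Analysis).
3. Who is interviewed: women diverse in race and relationship length; attendance and technical difficulty are not named.
4. Items 1 and 2 share a platform, and item 3 does not deliberately bring in the women most affected. If technical trouble changes the chance of being interviewed at all, it lowers it, so the direction is under-representation.

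**Illustration of size**

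Inputs: n = 7 pretesters (from the article); k = number with connection, device or privacy problems (assumed); r = probability that an affected woman completes the Zoom interview (assumed, independent between women). Unaffected women are taken as always reached.

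- Chance that no affected woman is heard: (1 − r)^k
- Affected share among interviewees, as a ratio of expected counts: k·r / (k·r + 7 − k)

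Example with k = 2 and r = 0.5: (1 − 0.5)² = 0.25, and 1.0 / (1.0 + 5) = 16.7%, against a true share of 2/7 = 28.6%.

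| k (true share) | r | Share among interviewees | Chance none is heard |
|---|---|---|---|
| 1 (14.3%) | 1.0 | 14.3% | 0% |
| 1 | 0.8 | 11.8% | 20% |
| 1 | 0.5 | 7.7% | 50% |
| 1 | 0.25 | 4.0% | 75% |
| 2 (28.6%) | 1.0 | 28.6% | 0% |
| 2 | 0.8 | 24.2% | 4% |
| 2 | 0.5 | 16.7% | 25% |
| 2 | 0.25 | 9.1% | 56% |

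The last column matters more here. The analysis is thematic and estimates no proportion, so the practical question is whether the problem is voiced at all.

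**The case against.** The case on the other side is substantial, and much of it stands.

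- **The same 7 women may all be interviewed.** The article uses the same description for pretesters and interviewees, and a domain on incomplete sessions makes sense only if women who had them are expected to be heard. This stands: nothing says that a subset is taken or that women who stopped are excluded. But inviting all 7 does not help a woman who cannot complete the call.
- **The recordings are a second source.** A reader might infer from the Data Analysis section that the recordings go unused. The article does not support that: "The sessions and group check-in will be video-recorded for analysis" states a use, and the details of scoring may sit in a fuller document. What remains is that the article gives the recordings no stated role in the usability themes.
- **There are other safeguards.** Missed sessions are followed up, data are paid for, and devices can be borrowed. These lower the risk. However, the follow-up is not described as usability data, a data plan does not cure weak signal or lack of privacy, and device support is stated for sessions only.
- **The obstacle is not identical.** Five weekly 2-hour group sessions ask more than one individual interview of about 50 minutes. Sessions are also missed for non-technical reasons, and a woman with intermittent drops can still describe them. This is why r may be well above zero.
- **The pilot would catch surviving faults.** Aim 2 adds Zoom training, a smartphone check, survey items on taking part in sessions, and interviews with all participants at three time points. This limits the consequence, though finding faults before the pilot is the purpose of usability testing.

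**Conclusion.** The point holds as a risk. The Zoom mode is a stated choice, the platform is what is being evaluated, and any resulting bias goes one way. The size cannot be taken from the article. With 2 of 7 women affected, the chance that neither is heard ranges from nil at full reach to 56% at a reach of 0.25, and these reach values are assumptions.

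Three stronger readings are tempting but unsupported:

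- **Technical problems will certainly be under-reported.** This predicts a reach that the article does not give. The limiting case, in which 2 of 7 are affected and interviews show 0 of 5, needs both affected women to have no chance of being interviewed and nobody else to meet a fault.
- **Women who stopped are excluded.** The text does not say so.
- **A favourable usability result clears SOAR for the pilot.** The article contains no go/no-go rule of that kind.

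This is an inexpensive improvement to a small formative step, not an error that invalidates it.

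**What to change.** 1. Offer each of the 7 pretesters, including any who missed sessions or stopped, a phone or in-person interview as an alternative to Zoom.
2. From the existing recordings and the attendance follow-up, tabulate late joins, drops and missed sessions for each session, and report the table beside the interview themes.
3. State how many pretesters were interviewed, by which mode, and how that compares with their attendance.

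The cost is a few calls or trips, at most 7 interviews in another mode, and a short tally. Travel reimbursement is already provided.

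The Results section says that tailoring ended in November 2023, so the interview mode may no longer be changeable for this group. Items 2 and 3 remain possible if the recordings and attendance records were kept. Item 1 can be carried into the further adaptation that the article foresees.
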